### Statistical analysis

Descriptive statistics will be used to assess clinicopathological characteristics. Mean values and standard deviation will be provided for continuous variables, whereas frequency and percentage distributions will be provided for categorical variables. Groups will be compared using the chi-square test for categorical variables and the Student’s *t*-test for continuous variables. The Kaplan–Meier and log-rank test method and log-rank test will be used to estimate and compare OS and PFS. Univariate and multivariate survival analyses will be conducted using the Cox proportional hazards model, which will provide hazard ratios (HRs) with 95% confidence intervals (CI). For subjects without endpoints or who violate the study protocol will be excluded. Statistical analysis will be performed using SPSS software (version 25.0; IBM, Armonk, NY) and R software [V.3.6.2 (http://www.R-project.org)]. The significance level will be set at *P* < 0.05, and all statistical tests will be two-sided.

Microbiome analyses will be conducted using 16S rRNA sequencing to determine the differences in alpha diversity among the three groups by calculating the Shannon, Chao1, and Simpson indices. Beta diversity will be generated using the weighted UniFrac distance and visualized using a principal component analysis plot. Between-group differences were analyzed using multivariate analysis of variance with permutation. Furthermore, subgroup analysis according to the number and location of metastasis will be performed.

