### Study timeline

After completing the recruitment procedure, clinical and pathological data were collected (Table 1).

**Table 1 Tab1:** Clinical and pathological data

Clinical data				Pathological data
Baseline	Surgery-related	ICI therapy-related	Oncological outcome	
Age	OR note (including any intraoperative events)	Dosage	Overall survival	Pathological TNM staging
Sex	EBL	Cycle	Progression-free survival	Cell type
Height	Surgical morbidity (according to CDC)	Toxicities (graded by CTCAE v5.0)	Objective response rate (according to RECIST v1.1)	ISUP nuclear grade
Weight		Total administration periods		
BMI		Cause of discontinuation		
BSA				
KPS				
IMDC risk feature				
Clinical TNM staging				
Metastatic sites				

*BMI* body mass index, *BSA* body surface area, *CDC* Clavien–Dindo classification, *CTCAE* Common Terminology Criteria for Adverse Events, *EBL* estimated blood loss, *IMDC* International mRCC Database Consortium, *ISUP* International Society of Urologic Pathologists, *KPS* Karnofsky Performance Status, *OR* operating room, *RECIST* Response Evaluation Criteria for Solid Tumors

A flowchart of the study is shown in Fig. 1. Patients will be evaluated for eligibility for surgery. If they are not eligible for surgery, they will start ICI therapy (induction phase). Then, they will be assessed for whether they are eligible for surgery. If not, they will continue with ICI therapy (maintenance phase) (Group C). If they are eligible for surgery, they will be randomly allocated to the deferred CN group (Group B) or ICIs only. If they are eligible for surgery at the first visit, they will be randomly allocated to the upfront CN Group A (group A) or the deferred CN group (Group B). Patients will be randomly allocated in a 1:1 ratio using a computer-generated allocation sequence by a local project nurse. The randomization will be performed on an institutional basis to prevent bias.

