### Sample size justification

Two prospective RCTs, PROBE (NCT04510597) and NORDICSUN (NCT03977571), are currently ongoing, but do not include an upfront CN arm. We determined the sample size based on the most recent real-world data that analyzed the intermediate/high risk group of mRCC patients stratified into upfront CN, deferred CN, and systemic treatment group [17]. To determine the required sample size for the study, we utilized two calculators for two-group survival analysis [18]. For Calculator 1, with a two-tailed alpha level (*α*) set at 0.05 and a beta level (*β*) of 0.2, along with a proportion of subjects in Group 1 (upfront and deferred CN) of 0.66 and a proportion in Group 0 (ICIs only) of 0.34, the relative hazard was set at 0.37. The calculated number of events needed to achieve 80% power was 35. For Calculator 2, with the total number of events set at 35, and assuming a baseline event rate of 0.53 and a median survival time in Group 0 (ICIs only) of 1.3 years, along with a censoring rate of 0.1 and a planned average length of follow-up of 5 years, the sample sizes required for each group were determined. Therefore, a total of 57 subjects were needed for the study.

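### OS is given a log-rank test and both univariate and multivariate Cox models, none named as primary; one Cox model adjusted for the baseline IMDC count, within randomisation stage, should be fixed in advance

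*Protocol article*

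**What the plan says.** All references are to the protocol article.

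- **Statistical analysis.** Kaplan–Meier curves and a log-rank test are planned for OS and PFS, with no strata named. In addition, "Univariate and multivariate survival analyses will be conducted using the Cox proportional hazards model", giving hazard ratios with 95% confidence intervals. No covariates are listed and no result is designated as the primary one. Further, "all statistical tests will be two-sided".
- **Study timeline.** Table 1 lists "IMDC risk feature" among ten baseline variables. On allocation, "The randomization will be performed on an institutional basis to prevent bias". Patients fit for surgery at the first visit are randomised between upfront and deferred CN. Those who become fit after induction are randomised between deferred CN and ICIs only.
- **Inclusion criteria.** IMDC features are described as prognostic factors and used to define who may enter.
- **Sample size justification.** The sizing is a plain two-group comparison with "a proportion of subjects in Group 1 (upfront and deferred CN) of 0.66"; "the relative hazard was set at 0.37" and "The calculated number of events needed to achieve 80% power was 35".

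**The concern.** Two things are at stake.

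First, the text promises a log-rank test, a univariate hazard ratio and one or more multivariate hazard ratios for the same endpoint, and ranks none of them. If they disagree, the choice of answer can be made after the data are seen. Ten baseline variables are available, so many multivariate models could be built on about 35 events.

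Second, the trial has almost no spare power. If the IMDC count is strongly related to survival, an unadjusted comparison estimates a diluted hazard ratio and is exposed to chance imbalance between small groups. The variable that would repair this is already being collected.

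**Working it through.** **1. The plan's own figures.** Inputs from Sample size justification: two-sided alpha 0.05, power 80%, hazard ratio 0.37, CN share 0.66.

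Events = (1.960 + 0.842)² / [0.66 × 0.34 × (ln 0.37)²] = 7.849 / (0.2244 × 0.9886) = 35.4, stated as 35. Power with 35 events is Φ(√(35 × 0.2244) × 0.994 − 1.960) = 79.6%.

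For N, take control hazard 0.53 per year, CN hazard 0.37 × 0.53 = 0.196, censoring 0.1 (read as a yearly rate) and 5 years. P(event) = λ/(λ + 0.1) × [1 − exp(−5(λ + 0.1))] gives 0.805 (control) and 0.512 (CN). Pooled: 0.34 × 0.805 + 0.66 × 0.512 = 0.611, and 35/0.611 = 57.2, stated as 57. Both figures reproduce for a comparison without covariates.

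**2. Cox power with and without adjustment.** There were 6,000 simulated trials per row, with 38 CN and 19 no-CN patients, control hazard 0.533 per year midway (on the log scale) between the IMDC levels, and a mean of 34.5 to 34.8 events. Assumed, because the document gives no figures: IMDC as two equally common levels with hazard ratio 1 to 3; three institutions with shares 60/25/15% and no institution effect. The 0.37 is taken as the treatment hazard ratio at a given IMDC level. Monte Carlo standard error is about 0.5 points.

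| IMDC HR (assumed) | Unadjusted | + IMDC | + IMDC + institution |
|---|---|---|---|
| 1 | 82.1% | 81.4% | 80.2% |
| 1.5 | 80.7% | 81.9% | 80.8% |
| 2 | 76.9% | 81.2% | 80.0% |
| 3 | 69.5% | 80.8% | 79.6% |

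IMDC adjustment changes power by −0.7, +1.2, +4.3 and +11.3 points. Adding institution then takes off 1.1 to 1.2 points in every row.

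**3. Log-rank power** (8,000 trials per row, allocation blocked within institution).

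| IMDC HR (assumed) | No strata | By IMDC | By institution |
|---|---|---|---|
| 1 | 82.8% | 81.4% | 80.7% |
| 1.5 | 81.0% | 80.2% | 78.6% |
| 2 | 78.0% | 81.0% | 76.5% |
| 3 | 70.6% | 79.5% | 69.0% |

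IMDC strata gain 3.0 points at HR 2 and 8.9 at HR 3, and lose about 1 point at HR 1.5 or below. Institution strata lose 1.5 to 2.4 points here. With an assumed institution effect (log hazard ratios −0.3, 0 and 0.3) they still lose 0.6 to 0.8.

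**4. Cost of an over-full model.** With no treatment effect, IMDC HR 2 and about 45 events, the Cox Wald test rejects in 5.3% of trials unadjusted, 5.7% with IMDC, 6.4% with IMDC and institution, and 7.3% with IMDC and five irrelevant covariates (standard error about 0.3 points). The 0.4-point difference between the first two is too small to account for the power gain at HR 2 or 3.

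**5. Chance imbalance.** For a level held by a share p of patients, the standard deviation of the difference in shares is √[p(1 − p)(1/38 + 1/19)]: 0.129 at p = 0.3 and 0.140 at p = 0.5. A difference of at least 15 points then has probability of about 24% to 29%. The shares are assumed.

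**6. Can IMDC vary among randomised patients?** The Abstract and Study design allow up to three features. Inclusion criteria ask for more than one. The text under Fig. 1 limits CN candidates to fewer than three. Taken literally, the last two leave exactly two features, and a constant cannot be adjusted for.

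**The case against.** The strongest objection is that strata, covariate lists and the naming of a primary model usually belong in a statistical analysis plan, which is not shown. That stands against any claim based on silence alone. A reader might infer that the plan prescribes an unstratified test; it does not say so, and a multivariate model is planned, so adjustment is not excluded. What survives rests on what is stated: several analyses are listed side by side for the primary endpoint, and one adjusted model is a demonstrably better choice in some plausible settings and costs little in the others.

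A reader might also infer that ignoring institution throws away power. The calculations show the opposite: institution strata lost power in every scenario. Moreover, the sentence on institutional randomisation may describe where allocation is carried out rather than a stratified sequence.

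It is also fair to object that an unadjusted log-rank test is valid and matches the way the trial was sized, and that the IMDC benefit depends on assumed effects. Both points stand, so the gain can only be stated conditionally.

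Finally, the simulations are not this trial's design. Upfront CN is never randomised against ICIs only, and patients who remain unfit for surgery enter the ICI group without randomisation. The power figures show what adjustment does; they are not the power of the within-stage analysis.

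**Conclusion.** The concern holds in a limited form. The protocol names no primary analysis for OS among those it lists, and a single IMDC-adjusted Cox model would be the better choice. Adjustment moves power by about 1 point either way at an IMDC hazard ratio of 1 to 1.5. It gains about 3 to 4 points at 2 and about 9 to 11 at 3, taking the log-rank and Cox results together. This rests on assumed IMDC effects, two equally common IMDC levels and one simple 66/34 randomisation.

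The documents do not support saying that the trial's power is below 80% as a matter of fact, because they give no IMDC effect. Nor do they support a new intermediate/poor stratification factor at randomisation. That class may not vary among randomised patients, and adding it would change the allocation procedure rather than only the analysis text.

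**What to change.** 1. Reconcile the Abstract, Study design, Inclusion criteria and Study timeline on the permitted number of IMDC features, so that it is known whether the count varies among randomised patients.
2. Before outcome data are seen, name one primary OS analysis: a Cox model with treatment and the baseline IMDC risk-feature count, run within randomisation stage (first visit or post-induction), so that each treatment contrast is one that was actually randomised. If the reconciled criteria leave the count constant, the IMDC term drops out and the rest stands.
3. Label the unadjusted log-rank test, the univariate Cox model and any other multivariate model as supportive.
4. Do the same for PFS.
5. Institution may be added as a covariate to reflect the allocation, accepting a loss of about 1 point of power in the Cox model; no power claim should rest on it.

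The cost is a change of analysis text, with notification to the IRB if it counts as a substantial amendment. No new data are needed, and recruitment is stated to run to December 2027, so there is time.

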### Primary endpoint

The primary endpoint is OS (in months) compared between patients receiving upfront CN, deferred CN, and ICIs only.

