#### Dropout criteria

If a subject fulfills any of the following dropout criteria, they will be discontinued from the middle of the study:

Patients who do not want to participate in the study.Patients who fall into the exclusion criteria during the study (such as the patients who need for starting systemic corticosteroids, antibiotics, investigational drugs, etc., during the study).Patients with severe side effects during the treatment and treatment can no longer be continued according to the schedule.Patients who do not adhere to the protocol of the study.

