### Adherence with study protocol

Non-adherence with the trial protocol will be reported and will be dropped out from the study.

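### The exclusion of subjects without endpoints and of protocol violators is wrong as written: no as-randomised population is stated, and read literally the rule drops about 22 of 57 patients from the OS analysis

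*Protocol article*

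**What the plan says.** All references are to the protocol article.

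- **Primary endpoint:** "The primary endpoint is OS (in months) compared between patients receiving upfront CN, deferred CN, and ICIs only".
- **Statistical analysis:** Kaplan-Meier and the "log-rank test will be used to estimate and compare OS and PFS", with Cox models for hazard ratios. The same paragraph then states: "For subjects without endpoints or who violate the study protocol will be excluded". The sentence is not confined to a per-protocol or secondary analysis.
- **Dropout criteria:** those discontinued partway through include "Patients who do not adhere to the protocol of the study", and also patients whose severe side effects prevent treatment on schedule.
- **Adherence with study protocol:** "Non-adherence with the trial protocol will be reported and will be dropped out from the study".
- **Sample size justification:** a two-group calculation, nephrectomy groups pooled against ICI only, with a censoring rate of 0.1 and 5 years of average follow-up.
- **Discussion:** follow-up is for at least 5 years or until death.

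No section says that patients are analysed as randomised.

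**The concern.** In a survival analysis, a subject who has not had the event still contributes time at risk up to the date of censoring. Excluding such subjects selects on the outcome. If one arm truly survives longer, that arm loses more patients and the estimated effect shrinks towards none.

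Excluding protocol violators is a second, separate selection made after randomisation. Surgery-related deviations can arise only in the groups assigned surgery, so this exclusion need not fall evenly across the arms.

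This is not detail left to an analysis plan. The article states a rule, and an analysis plan that follows it inherits the defect.

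**Working it through.** **Inputs (Sample size justification).** Two-sided alpha 0.05, beta 0.2; "proportion of subjects in Group 1 (upfront and deferred CN) of 0.66" and 0.34 for ICI only; relative hazard 0.37; 35 events; baseline event rate 0.53 per year (ln 2 / 1.3 = 0.533); censoring rate 0.1, read as per year; follow-up 5 years; N = 57.

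**Step 1: reproduce the plan's figures.**

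- Events (Schoenfeld): (1.960 + 0.842)² / (0.66 × 0.34 × (ln 0.37)²) = 7.849 / (0.2244 × 0.9885) = 35.4. The plan has 35.
- Probability of an observed death, with exponential survival and censoring: P = λ/(λ + c) × (1 − exp(−(λ + c) × 5)).
  - ICI only, λ = 0.53: 0.841 × 0.957 = 0.805.
  - Nephrectomy groups, λ = 0.37 × 0.53 = 0.196: 0.662 × 0.772 = 0.512.
  - Weighted: 0.34 × 0.805 + 0.66 × 0.512 = 0.611.
- N = 35 / 0.611 = 57.2. The plan has 57.

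The stated N is therefore built on event-free subjects contributing censored time.

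**Step 2: who is dropped on the literal reading (no death).**

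- ICI only: 57 × 0.34 × (1 − 0.805) ≈ 3.8, or 19% of that group.
- Nephrectomy groups: 57 × 0.66 × (1 − 0.512) ≈ 18.4, or 49%.
- Total: about 22 of 57.

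**Step 3: effect on the estimate.** 10,000 simulated trials of 38 versus 19 on these inputs:

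| Analysis | True HR | Median estimated HR | Rejection rate |
|---|---|---|---|
| All subjects, event-free censored | 0.37 | 0.37 | 83% |
| Subjects with a death only | 0.37 | 0.64 | 24% |
| All subjects, event-free censored | 1 | 1.00 | 5.1% |
| Subjects with a death only | 1 | 1.00 | 5.7% |

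(Schoenfeld's approximation gives 79% at the 34.9 events expected, against the simulated 83%.) Among deaths only, median survival is about 1.1 years (ICI only) and 1.7 years (nephrectomy). The true medians are ln 2 / 0.53 = 1.3 and ln 2 / 0.196 = 3.5 years.

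**Step 4: the narrower reading (no outcome data).** Subjects expected to be alive and under follow-up at 5 years number 57 × 0.34 × exp(−0.63 × 5) ≈ 0.8 and 57 × 0.66 × exp(−0.296 × 5) ≈ 8.6, about 9.4 in all. The other event-free subjects, about 22.1 − 9.4 = 12.7, are censored earlier. That is the most this reading could drop, if every one of them counted as having no outcome data. They should be censored at last contact.

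**Step 5: excluding violators.** The article gives no violation rate, so a range is assumed.

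- Unrelated to outcome, 5% to 30% of subjects: expected events fall from 34.9 to between 33.1 and 24.4, and power to between 77% and 64%.
- Related to outcome: suppose deferred-nephrectomy patients who die or are censored before surgery are classed as violators (an assumption), and there is no true effect. Under Study timeline, deferred nephrectomy versus ICI only is randomised after induction, with surgery within 6 weeks. At a combined rate of 0.63 per year, 1 − exp(−0.63 × 6/52) = 7% of the deferred group is removed. The median estimated HR is then about 0.92 (19 versus 19), with a rejection rate of 6.1% against 5.8% with no exclusion. In the pooled 38 versus 19 comparison it is about 0.96.

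**The case against.** The sentence is ungrammatical, and its first half may mean subjects with no outcome data. The rest of the article favours that: the sizing allows for censoring, the named methods handle it, and follow-up is for at least 5 years or until death. A reader might infer that the sponsor plans a deaths-only analysis. The documents do not establish that, so the 22 of 57, the HR of 0.64 and the 24% power hold only for the literal reading. The narrower reading does not rescue the rule, because subjects lost to follow-up belong in the analysis as censored.

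A reader might also infer that excluding violators creates a sizeable false benefit for surgery. With a window of about 4 months (0.33 years) before surgery, the same simulation gives a null HR of 0.81 and a rejection rate of 9.0% against 5.5%. That window does not fit the design. It applies to deferred patients randomised at the first visit, whose randomised comparator is upfront nephrectomy; against ICI only, deaths during induction precede randomisation. No section says that dying before surgery counts as a violation, and the entry criterion of more than 4 months' life expectancy should make very early deaths fewer. The 0.81 is a worst case for a comparison the trial does not set up.

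Nor do the calculations support saying that the type I error fails under every reading. Dropping survivors when censoring is equal leaves it at about 6%; that harm is attenuation and lost power.

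What stands against the objection: the exclusion is written without limit, two other sections reinforce it, and no as-randomised population is stated.

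**Conclusion.** The rule is wrong as written and should be corrected before analysis. Two parts hold under any reading: subjects who should be censored are dropped, and violators are removed after randomisation, which breaks the randomised comparison.

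The large figures (HR 0.37 to 0.64, power 83% to 24%) are conditional on the literal reading and on the plan's own exponential inputs, with 0.1 taken as a yearly censoring rate. The outcome-related bias from excluding violators is modest where it can be sized (null HR about 0.92, or 0.96 pooled) and rests on an assumed definition of a violator. Exclusions tied to toxicity could add bias that is not quantified here.

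**What to change.** Replace the exclusion sentence in Statistical analysis with wording such as:

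> The primary OS and PFS analyses include every randomised patient in the group assigned, regardless of surgery performed, treatment received or protocol deviation. Patients without the event are censored at last date known alive (OS) or last adequate assessment (PFS). A per-protocol analysis is a sensitivity analysis.

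Amend both Dropout criteria and Adherence with study protocol so that stopping study treatment or non-adherence does not end OS follow-up unless consent is withdrawn. Changing only one of them would still let follow-up be lost.

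State that patients placed in Group C without randomisation (Study timeline: those still ineligible for surgery after induction) are reported separately from the randomised comparison. Otherwise the new wording leaves them without an analysis role.

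The cost is an amendment to three existing sections and one added statement, plus continued survival follow-up of patients who would otherwise leave the study. The stated N need not change, since it already assumes that event-free subjects are kept and censored. Recruitment is stated to run to December 2027, so there is time to do this before analysis.

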#### Group-specific criteria

Group A: Upfront CN: cytoreductive nephrectomy ± metastasectomy, followed by induction therapy with nivolumab plus ipilimumab, and maintenance therapy with nivolumab.

Group B: Deferred CN: cytoreductive nephrectomy ± metastasectomy after induction therapy with nivolumab plus ipilimumab, followed by maintenance therapy with nivolumab.

Group C: No surgery: induction therapy with nivolumab plus ipilimumab followed by maintenance therapy with nivolumab.

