**Fig. 1 Fig1:**
[figure not shown]
Study flowchart. CN, cytoreductive nephrectomy; IMDC, International mRCC Database Consortium; Ipi, ipilimumab; mRCC, metastatic renal cell carcinoma; Nivo, nivolumab; KPS, Karnofsky performance status

Candidates for CN are patients with good performance status (Karnofsky performance status ≥ 80%) and less than three IMDC risk features and whose primary tumor could be surgically removed. Metastasectomy can be performed when the metastatic sites can be surgically removed. All patients eligible for ICI therapy will receive four cycles of intravenous nivolumab (3 mg/kg) plus ipilimumab (1 mg/kg) every 3 weeks as the induction phase, followed by a response evaluation. After the induction phase, intravenous nivolumab (3 mg/kg) will be administered 6 times every 2 weeks as the maintenance phase, followed by response evaluation. Nivolumab monotherapy will be maintained for a maximum of 2 years for those without adverse side effects. During ICI therapy, adverse events will be evaluated once per cycle. Patients will discontinue ICI therapy when they develop serious adverse events, including grade 3 or worse, according to the Common Terminology Criteria for Adverse Events version 5.0 (CTCAE v 5.0). In the upfront CN group, the induction phase will be within 6 weeks of surgery, whereas in the deferred CN group, surgery will be performed within 6 weeks of the induction phase. The study will be conducted over a period of 5 years.

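### Excluding protocol violators and patients without endpoints means OS and PFS need not be compared as randomised, and the resulting bias can go either way

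*Protocol article*

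**What the plan says.** The exclusion rule comes shortly after the log-rank and Cox methods for OS and PFS in the Statistical analysis section: "For subjects without endpoints or who violate the study protocol will be excluded". The article names no intention-to-treat set. Two further sections point the same way. Dropout criteria lists "Patients who do not adhere to the protocol of the study" among those to be discontinued, and Adherence with study protocol adds "Non-adherence with the trial protocol will be reported and will be dropped out from the study".

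What counts as following the protocol differs by arm. Study timeline randomises patients who are surgical candidates at the first visit to Group A (upfront nephrectomy) or Group B (deferred). Group-specific criteria defines Group B as nephrectomy with or without "metastasectomy after induction therapy with nivolumab plus ipilimumab, followed by maintenance therapy with nivolumab". The text under Fig. 1 limits nephrectomy to patients with Karnofsky status of at least 80%, "less than three IMDC risk features and whose primary tumor could be surgically removed". The same text gives each surgical arm a time limit. Group A must start induction within 6 weeks of surgery, "whereas in the deferred CN group, surgery will be performed within 6 weeks of the induction phase". Neither limit carries an exception.

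**The concern.** Both limits apply after randomisation, and whether a patient meets them depends on how the patient is doing. A Group B patient must stay operable through four 3-weekly cycles and up to 6 further weeks, so up to 4 × 3 + 6 = 18 weeks from the start of immunotherapy. A Group A patient must recover from surgery well enough to start induction within 6 weeks. Patients who fail either requirement plausibly have a worse prognosis. If they are classed as violators and removed, the arms left for analysis are no longer those that randomisation made comparable.

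OS is the primary endpoint, and A versus B is the randomised comparison of surgical timing, a question the article says the trial will help answer. The clause on patients without endpoints adds a second problem. It does not say whether it means patients with no outcome data or patients who have not had an event. The latter should be censored, not excluded.

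**Working it through.** **1. The plan's own figures.** Sample size justification gives a hazard ratio of 0.37, two-sided alpha 0.05, power 80%, shares 0.66 and 0.34, baseline rate 0.53 (control median 1.3 years; ln 2 / 1.3 = 0.533), censoring rate 0.1 and 5 years of follow-up.
- Events: (1.960 + 0.842)² / (0.66 × 0.34 × (ln 0.37)²) = 35.4 (stated: 35).
- Event probability: λ/(λ + 0.1) × (1 − exp(−5(λ + 0.1))). This is 0.805 at λ = 0.53 and 0.512 at λ = 0.53 × 0.37. The weighted mean is 0.34 × 0.805 + 0.66 × 0.512 = 0.611.
- N = 35 / 0.611 = 57 (stated: 57).

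The stated size reproduces and is not in dispute. It concerns both nephrectomy groups pooled against immunotherapy alone. No power is stated for A versus B.

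**2. Illustration of the Group B route alone.** The documents give no loss fraction and no hazard for such patients, so both are assumed. A fraction f of each arm is of the kind that loses candidacy and has m times the hazard of the rest. The mean hazard is held at 0.533 × 0.37 = 0.197 per year, so the majority's hazard is b = 0.197 / (1 − f + fm). The true A–B hazard ratio is 1, with 1:1 arms and 5 years of follow-up. Only Group B patients of this kind who are alive at 3 months are removed, because those who die earlier never reach the surgical decision. The large-sample Cox hazard ratio θ solves ∫[dB − (dA + dB) × θY_B / (Y_A + θY_B)] = 0, where Y is the fraction at risk and d the event density in each arm. With the censoring rate of 0.1:

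| | f = 0.1 | f = 0.2 | f = 0.3 |
|---|---|---|---|
| m = 2 | 0.95 | 0.90 | 0.86 |
| m = 3 | 0.92 | 0.84 | 0.77 |

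Leaving out the censoring rate changes these by less than 0.01. Setting the majority's hazard, instead of the mean, at the planned rate gives 0.81 to 0.95. With m = 1 (no worse prognosis) the ratio is 1.01 to 1.04, so there is no shift towards B.

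**3. Adding the Group A route.** If the same kind of patient is also removed from A under the same 3-month rule, the ratio is 1.00. If all of that kind are removed from A, including early deaths, it is 1.02 to 1.10. If they are removed from A only and kept in B, it is 1.05 to 1.29 under the 3-month rule. Analysed as randomised, it is 1.00.

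**4. Precision.** A plus B holds at most 57 × 0.66 = 37.6 patients.
- f = 0.1, m = 2: b = 0.1973 / 1.1 = 0.179. Event probability 0.9 × 0.483 + 0.1 × 0.703 = 0.505, so 19.0 events.
- f = 0.3, m = 3: b = 0.1973 / 1.6 = 0.123. Event probability 0.7 × 0.371 + 0.3 × 0.712 = 0.474, so 17.8 events.

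The 95% interval factor exp(1.96 × √(4/D)) is 2.46 at D = 19.0 and 2.53 at D = 17.8. The first-visit A–B randomisation is smaller still, because Study timeline also places patients randomised after induction in Group B.

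**The case against.** The strongest reply is that no sentence calls it a violation to omit nephrectomy in a Group B patient who is no longer a candidate. The text under Fig. 1 reserves surgery for candidates, its maintenance schedule is not restricted by arm, and the Discussion promises follow-up until death. Not operating on a non-candidate could therefore count as compliant. The full protocol or a statistical analysis plan may define violations, and the flowchart is not shown. This stands as far as it goes: exclusion of these patients is a permitted reading, not a certainty. It does not remove the point, because the exclusion of violators is itself stated, and a later plan would have to contradict it.

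A reader might go further and infer that the rule biases A versus B in favour of deferred nephrectomy. The documents do not support a fixed direction. Group A's 6-week limit is as unconditional as Group B's and opens a parallel route to exclusion. The dropout criterion "Patients with severe side effects during the treatment and treatment can no longer be continued according to the schedule" does not supply a direction either: it requires severe side effects, and both arms receive the same induction.

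It is also fair to say that the sample size rests on a different contrast, and that imprecision in A versus B would exceed most of this bias. In a simulation with 19 patients per arm and m = 3, two-sided type I error rose only from about 4% to 5–6%. The harm is mainly a distorted estimate.

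**Conclusion.** The concern holds in this form: the stated exclusions allow OS and PFS to be compared in a subset selected by prognosis-linked events after randomisation, and the selection can differ by arm. The net direction and size are not fixed by the documents. The hazard ratios of about 0.77 to 0.95 illustrate one route taken alone. They rest on an assumed 10 to 30% of patients with 2 to 3 times the hazard, no true difference, and no corresponding removal from Group A. Comparable removal from A brings the ratio back to 1.00 or slightly above. Set against an interval factor of about 2.5 either side, the bias would be hard to see in the data, so it should be prevented in the plan. Confidence is medium, because how unoperated Group B patients or late-starting Group A patients would be classified is left open.

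**What to change.** - **Statistical analysis:** replace the exclusion with a rule that OS and PFS are analysed for all randomised patients in the arm assigned, whether or not nephrectomy or immunotherapy was given as planned, and that patients without an event are censored at last follow-up.
- **Dropout criteria and Adherence with study protocol:** state that stopping study treatment or non-adherence does not end follow-up for survival and progression, unless the patient withdraws consent to follow-up.
- **Text under Fig. 1:** state that omitting nephrectomy in a Group B patient who no longer meets the surgical criteria, or delaying or omitting immunotherapy in Group A for medical reasons, is not a reason for exclusion.

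Apply the rule to all arms. Protecting only one arm would create the imbalance it is meant to prevent. A per-protocol analysis can stay as a sensitivity analysis.

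The cost is wording. The response evaluation after induction and follow-up until death are already planned, and recruitment runs to December 2027, so the rule can be settled before analysis. The drawback is some dilution of the contrast in treatment actually received, which the per-protocol analysis would help describe.
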